## Abstract

Osteoarthritis (OA) knee is one of the most common chronic degenerative conditions that imposes clinical and economic burdens on individuals and societies worldwide. Previous studies showed vitamin D levels correlated positively with lean muscle mass and grip strength, implying that vitamin D supplementation may improve muscle health in knee OA subjects. This randomized controlled trial (RCT) aims to compare the effects of vitamin D supplementation on knee muscle strength, physical function, pain, and sarcopenia status in patients with end-stage knee OA. Patients and outcome assessors will be blinded to group allocation. Fifty-six end-stage knee OA patients with vitamin D insufficiency fulfilling our inclusion criteria will be invited to participate in this study. Patients will be randomly assigned to take vitamin D supplementation (4,000 IU capsule daily) or placebo for six months. Measurements will be taken at baseline, three and six-month after the commencement of the vitamin D supplement, and 6-month after the interventional period. The primary outcome includes the isometric quadriceps and hamstring muscle strength measured by a hand-held dynamometer. Secondary outcomes include pain, performance-based and self-reported physical function and sarcopenia status. The success of this study will provide scientific evidence of whether the relatively cheap and well-tolerated vitamin D supplement can improve quadriceps muscle strength, physical function, pain symptoms, and sarcopenia status of this increasingly large population for end-stage knee OA patients. The study has great clinical significance given Hong Kong’s lengthy and growing waiting list for complete knee replacement procedures.

**Trial registration:** The trial was registered on clinicaltrials.gov (NCT05981534) on 31^st^ July 2023.

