### Outcomes and outcome assessments

The primary outcomes will be muscle strength using quadriceps and hamstring muscle assessments, and the secondary outcomes will be the post-intervention change in muscle strength function from baseline using 5-time chair stand test, sarcopenia assessment by Dual Energy X-ray Absorptiometry (DXA), handgrip strength and 6-meter gait speed test, six questionnaires: Western Ontario and McMaster Universities Osteoarthritis Index (WOMAC), Knee Injury and Osteoarthritis Outcome Score (KOOS), Short-Form 36 (SF-36), International Physical Activity Questionnaire (IPAQ), Nutritional Intake and Sunlight Exposure questionnaire (Questionnaires can be seen in S5 File), and biochemical assays including serum Vitamin D level and myokines. Blood samples will be taken under non-fasting conditions. The serum obtained will be immediately stored at -80°C until analysis.

Outcome assessments of the patients will be performed at baseline (0 month), 3 months and 6months after the commencement of vitamin D supplement, and 6-month after the interventional period.

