#### Knee muscle strength

The primary outcome will be obtained by measurement of knee muscle strength using a hand-held dynamometer (Hoggan Scientific, Salt Lake City, UT, USA) to assess maximal voluntary quadriceps and hamstring muscle strength. Each participant will be placed on an examination table with their feet elevated and their knees bent at a 60°. The maximal voluntary quadriceps muscle strength on the anterior aspect of the distal tibia (see Fig 3) and the maximal voluntary isometric hamstring muscle strength will be measured using the hand-held dynamometer placed on the posterior portion of the lower leg (see Fig 4). For stability, participants will hold onto the examination table with their hands. They will then be told to flex or extend their knee "as hard as possible" into the hand-held dynamometer. For five seconds, participants will keep applying force to the hand-held dynamometer, and the maximum force they can muster during the experiment will be noted. All tests will involve maximal voluntary isometric contractions. Both limbs will be assessed to record. Two testing trials will be completed. The maximum knee extensor and flexor strength were calculated to obtain an overall muscle strength value (kgf) divided by the patient’s body mass.

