### Sample size calculation

Based on our power calculation, we aim to recruit 28 patients for both groups, with a total of 56 participants. Quadriceps muscle strength measured by the handheld dynamometer will be the primary outcome for sample size estimation. The effect size of the isometric quadriceps muscle strength has been determined as 0.34 in patients with knee OA [36]. A repeated-measures one-way analysis of variance (ANOVA) will be used to compare knee muscle strength, muscle mass, physical functional test, biomarkers, and questionnaire score for four timepoints (before the vitamin D supplementation (Baseline), at 3months, 6 months, and 12 months after the commencement of vitamin D supplementation). When the sample size is 23 per group with 4 repeated measurements, will have 80% of the power to detect at the 0.05 significance level. An additional 20% will be added to account for possible attrition. Thus, our sample size of 28 participants per group (total *n* = 56) will be sufficient to achieve our objective. The sample size was calculated using G*Power 3.0 software.

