### Statistical analysis

Data in this study will be analyzed according to the intention-to-treat principle. Only the full analysis set and per-protocol set will be used for primary outcome analysis. The last observation carried forward (LOCF) will be used to impute the missing data by replacing it with the last observed value.

Quantitative variables will be expressed as mean ± standard deviation. Normality tests will be performed to determine whether the data is normally distributed. A one-way analysis of covariance (ANCOVA) tests with Bonferroni correction and with the baseline value as a covariate was conducted at 3m,6m, and 12m to determine the group effect on each parameter. Independent T-test (two-tailed) are used for multiple testing of continuous variables. Whereas the Chi-square test will be used to compare the proportions of categorical variables and to calculate the differences in the count data. A repeated measure analysis of variance (ANOVA) will be used to analyze the trend of changes in the scores among four-time points (Baseline, 3m, 6m, 12m) to determine the group×time effects. Post hoc analysis with Bonferroni correction will be conducted to explore the differences between baseline and 3m, baseline and 6m, 6m and 12m. The statistical analysis will be performed using commercialized statistical software (SPSS, version 29.0, IBM). All statistical significance is defined as P < 0.05.

Additional analyses will include subgroup analyses to estimate treatment effects for both female and male participants, normal BMI and overweight or obese participants.

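### Two strength measures are primary and are tested by three procedures over three follow-up visits, with no primary visit or test named, so error on the primary outcome is not held at 5%

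*Protocol article*

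**What the plan says.** **The measure.** The Abstract states: "The primary outcome includes the isometric quadriceps and hamstring muscle strength measured by a hand-held dynamometer". Outcomes and outcome assessments agrees, in the plural: "The primary outcomes will be muscle strength using quadriceps and hamstring muscle assessments". The Knee muscle strength section adds: "The maximum knee extensor and flexor strength were calculated to obtain an overall muscle strength value (kgf) divided by the patient’s body mass". This can be read as one combined value. The Sample size calculation uses one muscle: "Quadriceps muscle strength measured by the handheld dynamometer will be the primary outcome for sample size estimation".

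**The visits.** Strength is measured at baseline, 3, 6 and 12 months. No section names a primary visit.

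**The tests.** The Statistical analysis section lists:
- ANCOVAs at 3, 6 and 12 months with baseline as covariate and a Bonferroni correction, without saying what the correction spans;
- t-tests: "Independent T-test (two-tailed) are used for multiple testing of continuous variables";
- a repeated-measures ANOVA over the four time points for group×time, followed by Bonferroni-corrected post hoc comparisons of baseline with 3 months, baseline with 6 months, and 6 with 12 months.

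**The analysis sets and threshold.** The section invokes intention-to-treat and then says: "Only the full analysis set and per-protocol set will be used for primary outcome analysis". It closes with: "All statistical significance is defined as P < 0.05".

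**The concern.** A confirmatory trial needs one result, or a stated family of results, on which its conclusion rests. Here two muscles, three follow-up visits and up to three procedures bear on the primary outcome, and nothing says which of them decides. A Bonferroni correction inside the ANCOVAs does not cover a second muscle unless it is stated to, and it does not cover the other procedures at all. The investigators could therefore pick the deciding result after seeing the data, and neither a positive nor a null conclusion would carry a known error rate.

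The post hoc comparisons add a separate difficulty. They contrast visits, not arms. The Study interventions section itself cites a trial in which knee extension strength rose 8–11% over 10 weeks of supplementation without a significant difference from placebo. A change over time therefore cannot show a treatment effect.

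**Working it through.** **1. The plan's own figure.** Inputs from the Sample size calculation: effect size 0.34, 4 measurements, 23 per group (N = 46), alpha 0.05, power 80%. Assumed, because not given: correlation ρ = 0.5 between measurements, and 0.34 read as Cohen's f. For the between-group main effect of a repeated-measures ANOVA:

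λ = N·f²·m / (1 + (m − 1)ρ) = 46 × 0.1156 × 4 / 2.5 = 8.51, which gives power 0.814.

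N = 46 is the smallest even total that reaches 80%, so 23 per group reproduces. Adding 20% gives 23 × 1.2 = 27.6, rounded to 28. The calculation fits a between-group main effect on quadriceps strength, whereas the Statistical analysis section uses that ANOVA for group×time. The sample size therefore does not settle which test is primary.

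**2. Simple bounds for independent tests.**
- Three ANCOVAs at 0.05/3: 1 − (1 − 0.0167)³ = 4.9%.
- The same for two muscles: 1 − (1 − 0.0492)² = 9.6%.
- Three uncorrected t-tests: 1 − 0.95³ = 14.3%.

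**3. Null simulation.** The real tests are correlated, so trials with no effect were simulated: 28 per arm, 20,000 trials per scenario, one limb and one analysis set. Correlations are assumptions: 0.5–0.9 between visits and 0.5–0.8 between muscles. ANCOVAs were tested at 0.05/3, and the t-tests (3, 6 and 12 months) and group×time at 0.05. The Monte Carlo standard error at 25% is √(0.25 × 0.75 / 20,000) = 0.3 percentage points.

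Chance of at least one positive result:

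| Procedures counted | Quadriceps only | Both muscles | Both plus combined value |
|---|---|---|---|
| Bonferroni ANCOVAs | 4.2–4.8% | 7.2–8.9% | 7.4–9.9% |
| Plus group×time | 6.8–7.7% | 11.0–14.1% | 11.2–15.1% |
| Plus t-tests | 14.0–15.9% | 22.0–27.5% | 22.4–28.9% |
| All three, ANCOVAs not corrected across visits | 19.0–20.6% | 28.8–34.3% | 29.2–36.0% |

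Of the combinations in the table, only the Bonferroni ANCOVAs on quadriceps alone stay within 5%.

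**4. Power under a single primary test.** Assume d = 2 × 0.34 = 0.68, correlation 0.5 and 28 per arm. One 6-month ANCOVA then has 82% power at 0.05 and 68% at 0.0167. The chance that at least one of the three Bonferroni ANCOVAs is significant is 92% if the effect is the same at every visit, and 73% if it is half as large at 3 and 12 months. A single test at 0.05 can therefore gain or lose power against the present plan.

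**The case against.** Several points on the other side have force.

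- **The t-test sentence is ambiguous.** It names no visit, contrast or outcome, and it sits beside the chi-square sentence like a generic list of tests by variable type. It may describe baseline comparisons, and that no correction applies is inferred from silence. This stands, and it is why a separate range without the t-tests is given. That range still exceeds 5%.
- **A reader might infer three rival definitions of the primary outcome.** The text does not go that far. The Abstract and the Outcomes section agree on two muscles. Sizing on one of two primary measures is not a competing definition. The Knee muscle strength sentence may only mean that each muscle's force is divided by body mass. What remains is two primary measures with no stated correction across them.
- **A reader might infer that every test is run at 0.05.** That is wrong for the ANCOVAs, which carry a Bonferroni correction. If it spans both visits and muscles, the ANCOVAs alone would hold 5%, but the other procedures would remain outside it.
- **A reader might settle on one figure, such as 28%.** The document gives no error rate and no correlations. Under Bonferroni across visits, a value that high arises only near the low-correlation end with every procedure counted.
- **Index knee and ranking of analysis sets** may be left to a fuller document, and intention-to-treat is at least named. They are not counted as defects here, though the fix should settle them.
- **The post hoc comparisons are described as exploratory**, and the ANCOVA is the stated test of the group effect. That is fair. The comparisons still cannot support a claim about treatment.

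**Conclusion.** The concern holds as a structural defect: two primary measures, no primary visit, no primary test, and no stated correction across muscles or procedures. This is how the article itself fixes the analysis, not detail left for elsewhere. If any positive result counts as success, the false-positive rate is about 14–29% when all three procedures test the primary outcome, and about 7–15% when the t-tests serve another purpose. The low end of each range is quadriceps alone; the high end is both muscles plus a combined value.

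The ranges rest on the assumed correlations, on a Bonferroni correction across the three visits, and on the any-positive rule, which the document does not state. If the ANCOVAs were not corrected across visits, the rates with all three procedures would be about 19–36%. A second limb and the per-protocol set were not simulated; counting them as further chances of success would raise the rates.

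**What to change.** Before the interim look planned at about 20% of participants, whose findings are to be shown at a conference, amend the plan to name one primary analysis:
- quadriceps strength, the measure on which the trial is sized;
- in one index knee, chosen by a rule written in advance. Eligibility requires grade 3 or above on at least one side and both limbs are recorded, so listed for surgery and worse cannot be assumed to mean the same knee;
- at 6 months, the end of supplementation;
- compared between arms by baseline-adjusted ANCOVA in the full analysis set at two-sided 0.05.

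This holds the false-positive rate at 5%. Alternatively, keep quadriceps and hamstring as co-primary at that visit at 0.025 each, which holds it at or below 5%.

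Make the other visits, any combined value, the group×time test and the per-protocol set secondary or supportive. State what the t-tests are for, and do not use unadjusted t-tests for follow-up values of the primary outcome. Replace visit-to-visit comparisons with between-arm contrasts of change.

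The cost is wording in the protocol and analysis plan. Hamstring strength, unless kept as co-primary, and the other visits lose primary status. Whether power rises or falls depends on how the effect varies over visits. Under the co-primary option, quadriceps power on the assumptions in the working would lie between the 68% and 82% shown there.

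### Subgroup effects by sex and BMI are planned under a blanket P < 0.05 rule with no treatment-by-subgroup interaction named; read by within-subgroup significance, a uniform effect would often look confined to one subgroup

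*Protocol article*

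**What the plan says.** The Statistical analysis section of the protocol article gives subgroups one sentence, which lists among the additional analyses "subgroup analyses to estimate treatment effects for both female and male participants, normal BMI and overweight or obese participants". The sentence before it, which closes the preceding paragraph, reads "All statistical significance is defined as P < 0.05" and makes no exception for subgroup results. The repeated-measures ANOVA is planned "to determine the group×time effects", and no other interaction appears in the section. Bonferroni correction is attached to the ANCOVA and to the post hoc time comparisons, but not to the subgroups.

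The Sample size calculation section gives 28 patients per group, 56 in total, and states "The effect size of the isometric quadriceps muscle strength has been determined as 0.34 in patients with knee OA". The randomization section describes 1:1 blocked allocation and mentions no stratification by sex or BMI.

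**The concern.** Whether an effect differs between women and men is a question about the difference between two effects. A significant result in one sex and a non-significant one in the other does not answer it, because each half has low power and the two P values can fall on opposite sides of 0.05 by chance. The section states a target (an effect in each subgroup) and a general significance threshold, but names nothing that would compare the subgroups.

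At stake is a secondary claim, such as a benefit confined to one sex or one BMI class, published from a trial in which the effect was the same in everyone.

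**Working it through.** **Inputs from the protocol article.** 28 per arm; significance level 0.05; two-sided, as stated for the t-test ("Independent T-test (two-tailed) are used for multiple testing of continuous variables"); effect size 0.34; 23 per group for 80% power with four measurements.

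**Assumptions.** The shares of women and men are not given, so splits from 50:50 to about 80:20 are used, equal in both arms. All 28 per arm are analysed, which fits intention-to-treat with last observation carried forward. The within-subgroup test is an unadjusted t-test at one time point.

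**Step 1: the plan's own figure and the meaning of 0.34.** The text is "When the sample size is 23 per group with 4 repeated measurements, will have 80% of the power to detect at the 0.05 significance level". For the between-group test of a repeated-measures ANOVA, with total N, m = 4 and correlation ρ = 0.5 (assumed; not stated), the noncentrality is λ = f²·N·m / (1 + (m − 1)ρ). With f = 0.34 and N = 46, λ = 0.1156 × 46 × 4 / 2.5 = 8.51, and power on (1, 44) degrees of freedom is 0.814. N = 44 gives 0.796, so 46 (23 per group) is the smallest even N that reaches 80%. The stated number therefore reproduces if 0.34 is Cohen's f. It does not reproduce as a standardised difference in a simple two-group comparison, where 0.34 needs 136 per arm. The allowance "An additional 20% will be added to account for possible attrition" gives 23 × 1.2 = 27.6, so 28. For two equal groups d = 2f, so the design effect is 2 × 0.34 = 0.68 SD.

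**Step 2: power within one subgroup.** With n per arm, the t-test has 2n − 2 degrees of freedom and noncentrality d·√(n/2). At d = 0.68 and n = 14 this is 0.68 × √7 = 1.80, giving power 0.41.

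**Step 3: exactly one sex significant under the same true effect.** Women and men are different patients, so the two tests are independent and P(exactly one) = p₁(1 − p₂) + p₂(1 − p₁).

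| Split per arm | 0.68 SD: power | 0.68 SD: exactly one | 0.5 SD: exactly one | 0.34 SD: exactly one |
|---|---|---|---|---|
| 14 / 14 | 0.41, 0.41 | 48% | 37% | 24% |
| 20 / 8 | 0.55, 0.25 | 53% | 39% | 24% |
| 22 / 6 | 0.60, 0.19 | 56% | 40% | 25% |

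For example, at 20 / 8 and 0.68 SD: 0.554 × 0.755 + 0.245 × 0.446 = 0.418 + 0.109 = 0.53.

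**Step 4: a second model.** Using the repeated-measures power function of step 1 within each subgroup (f = 0.34, ρ = 0.5), exactly one subgroup is significant in 48% to 64% of trials with 56 patients and 50% to 61% with 46. In simulation, at least one of the two factors is discordant in 64% to 78% of trials.

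**Step 5: comparison.** Under the same uniform effect, an interaction test at 0.05 is positive in about 5% of trials (simulated 4.9% to 5.1%).

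**Step 6: no effect at all.** Testing the four overlapping subgroups at 0.05 gives at least one significant result in about 17% of trials (70% women and 60% overweight or obese assumed).

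**The case against.** The strongest reply is that the text does not say what a critic fears. It says estimate, not test. It calls the analyses additional, and it neither names nor excludes an interaction term. Subgroup estimates could come from an interaction model, and an analysis plan or full protocol that is not shown may say so. The threshold sentence belongs to the paragraph on the main tests, and no sentence commits the authors to a subgroup claim from separate P values. The subgroups are also few and named in advance.

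Most of this stands. A reader might infer that the plan has chosen separate significance testing in place of an interaction test, or that a claim of benefit in women but not in men is its likely conclusion. The document supports neither. The first reads a decision into silence. The second assumes an inference that the plan never states, and it is also smaller than the discordance figures suggest: at 0.68 SD, significance in women alone occurs in 24% of trials at 50:50 and, with women the larger group, about 42% at 20 / 8 and 48% at 22 / 6.

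What does not stand is that there is nothing to correct. The section fixes the target as an effect in each subgroup, applies its threshold to all results, and spells out an interaction where it wants one (group by time). Applied as worded, it leaves discordant P values as the available way to compare subgroups.

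The size also depends on the effect. If 0.34 were a standardised difference rather than Cohen's f, the discordance would be about 24% and not about half. Baseline adjustment, which the protocol names for the group effect, would change the powers too.

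**Conclusion.** The point holds as a conditional one. The protocol article plans subgroup effects under a general P < 0.05 rule and names no treatment-by-subgroup interaction. If the results are read by within-subgroup significance, a uniform effect would look confined to one sex in about 48% to 56% of trials at 0.68 SD, 37% to 40% at 0.5 SD and about 24% at 0.34 SD. All of these are several times the 5% of an interaction test. They rest on 28 analysed per arm, assumed splits of 50:50 to about 80:20 and an unadjusted t-test; 0.68 SD further rests on reading 0.34 as Cohen's f, which is the reading that reproduces 23 per group.

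It does not follow that the authors rejected an interaction test or will claim a sex-specific benefit. Severity is minor, because these analyses do not decide the primary conclusion.

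**What to change.** Replace the subgroup sentence with one stating that:

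- differences in effect by sex and by BMI group will be judged by group-by-sex and group-by-BMI terms in the baseline-adjusted ANCOVA of all patients;
- the interaction estimates, and the subgroup effects taken from that model, will be reported with confidence intervals as exploratory;
- the P < 0.05 rule does not apply to subgroup results, and no within-subgroup significance claim will be made.

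The cost is wording only: no new data, visits or patients. The article reports recruitment as ongoing and says the code stays unbroken until database lock, so the rule can still be set in advance.

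The downside is imprecision. Without covariate adjustment, the standard error of the group-by-sex term at 14 / 14 per arm is √(2/14 + 2/14) = 0.53 SD, so a 95% interval reaches about 1.07 SD either side (t = 2.007 on 52 degrees of freedom). At 20 / 8 the standard error is √(2/20 + 2/8) = 0.59 SD. Most interaction results will be inconclusive, and the report should say so.
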